#### Electronic Database

An e-database will be created to capture all the important variables required for the final study report and supervised by the CRO. Access to e-database will be limited to the site investigator (only for the particular site), study co-ordinators and project team and CRO, and will be password protected. The CRO will be responsible for the security and back up of the study e-database. The database will be checked for missing data and inconsistencies by the CRO from time to time in close liaison with the site investigator. The CRO will lock the database after informing the clinical coordinator and sponsor and then submit copy for statistical analysis and report writing both for interim and final report.

#### Trial Care and Record Retention

The participants will be advised to continue the usual protective measures like physical distancing, respiratory and hand hygiene, and wearing masks. They will be advised to follow guidelines of Ministry of AYUSH for COVID-19 prophylaxis. All clinical study documents will be retained by the investigator for at least 5 years after the study and await instructions of their final disposal from the sponsor. All protocol amendment will be approved by the respective Ethics Committees before implementation. In the event of an emergency of any type, medical or otherwise, the site investigator will inform the appropriate Ethics Committee, CRO, study coordinators and sponsor within 24 h. The Sponsor (CCRAS) will provide insurance coverage with respect to any liability caused by the investigational products (Ashwagandha) and or study related procedures in connection with the clinical study. The terms and conditions will apply as specified in the insurance policy document. The quantum of compensation for the Serious Adverse Events leading to the death will be given to the study participant/patients' nominee as per recommendations of the EC, DSMB, and as per the regulatory guidelines.

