## Abstract

**Introduction:**

Vaccines have emerged as the most effective tool in the fight against COVID-19. Governments all over the world have rolled out the COVID-19 vaccine program for their populations. Oxford-AstraZeneca COVID-19 vaccine (COVISHIELD™) is widely used in India. A large number of Indian people have been consuming various traditional medicines in the hope of better protection against COVID-19 infection. Several studies have reported immunological benefits of *Withania somnifera* (Ashwagandha) and its potential as a vaccine adjuvant. We propose to study the safety, immunogenicity and clinical protection offered by a 6-month regimen of Ashwagandha in participants who volunteer to be vaccinated against COVID-19 (COVISHIELD^TM^) in the ongoing national program of vaccination.

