#### Exclusion Criteria

Any known co-morbidity or acute illness with or without symptoms at the discretion of the investigator; History of known hypersensitivity to any component of the study material (Ashwagandha); Any confirmed or suspected condition with impaired/altered function of the immune system or conferring a possible risk suggested by investigations (e.g., increased levels of D-dimer); Women who are breast-feeding and pregnant; Individuals who are using any intervention (AYUSH or otherwise) for prophylaxis or for immune boosting or that may influence immune system e.g., steroids, methotrexate, anti-rheumatoid agents, drugs from AYUSH systems within 30 days prior to screening; Individuals who have received systemic immunoglobulins or blood products within 3 months prior to screening.

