#### Trial Intervention

The study includes two arms as Ashwagandha and Placebo The participants from placebo arm will have immunogenic effects only of vaccine, whereas participants in Ashwagandha arm may have additional safety, immunogenicity and protection from disease. Thus, the placebo arm will serve as a control to ascertain adjuvant effects offered by Ashwagandha.

Arm 1: Ashwagandha tablets (*n* = 600): Dose of Ashwagandha prescribed for this study is one tablet of the standardized aqueous extract equivalent to 4 gm Ashwagandha root powder per day administered within 7 days of the first or second dose of vaccine and continued up to 24 weeks. Each tablet used in this trial shall contain aqueous extract equivalent to 4 grams Ashwagandha root powder.

Arm 2: Placebo (*n* = 600): One placebo tablet will be administered daily beginning within 7 days of the first or second vaccine dose and continued up to 24 weeks. The appearance and weight of placebo tablet (containing microcrystalline cellulose) will be same as that of Ashwagandha tablet.

One tablet of Ashwagandha or placebo will be administered daily (on empty stomach in the morning) with water. Quality of Ashwagandha roots is ensured in accordance with prescribed pharmacopeia standards (19).

A window period of 7 days will be allowed on either side of the scheduled visit for exceptional or any other anticipated reasons at the discretion of the investigator.

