#### Concomitant Medication

As a general principle, concomitant medication of any kind will be kept to a minimum and will necessarily require clearance from a primary care physician and with full information provided to the study physician. All concomitant medication will be recorded in the study case record form (CRF) by the study physician. All complete CRFs/eCRF duly signed by the investigator and counter signed by principal investigator will be submitted within 2 weeks of the completion of the study to the Chief Clinical Coordinator. Although the study includes healthy participants, the medication required for any new illness during the study will be taken under supervision of the primary care physician and meticulously recorded in the participant CRF. Participants will be permitted general symptomatic medications like paracetamol and non-steroidal anti-inflammatory drugs for short period (<4 days) and including for any untoward mild to moderate symptoms like headache and body aches following vaccination. Patients will be carefully explained not to consume any other herbal and home remedies. Patients will be advised not to use any kind of food and nutrition supplement. Similarly, participants will be advised not to consume any kind of vitamins and/or minerals without a specific advice of physician.

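### All participants are advised to follow Ministry of AYUSH COVID-19 prophylaxis guidance, with no limit that squares this with the on-study bar on other herbal remedies and supplements

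*Protocol article*

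**What the plan says.** Four parts of the protocol article bear on this.

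- **Trial Care and Record Retention.** One sentence advises distancing, respiratory and hand hygiene, and masks. A separate sentence then adds: "They will be advised to follow guidelines of Ministry of AYUSH for COVID-19 prophylaxis". It has no exception and does not say which elements of the guidelines are meant.
- **Concomitant Medication.** "Patients will be carefully explained not to consume any other herbal and home remedies" and "Patients will be advised not to use any kind of food and nutrition supplement". Vitamins and minerals need a physician's specific advice. For record keeping, "All concomitant medication will be recorded in the study case record form (CRF) by the study physician".
- **Exclusion Criteria.** The people excluded include "Individuals who are using any intervention (AYUSH or otherwise) for prophylaxis or for immune boosting or that may influence immune system", and the examples given end with "drugs from AYUSH systems within 30 days prior to screening".
- **Trial Intervention.** The control is described thus: "The participants from placebo arm will have immunogenic effects only of vaccine". The placebo arm is the reference against which any adjuvant effect of Ashwagandha is judged.

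**The concern.** Two instructions to participants are both in print and can point in opposite directions. A participant whose AYUSH guidance recommended a herbal preparation would be advised to take it by one section and told not to by another. The article does not say which rule wins.

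The subject matter makes this more than loose wording. The primary outcome is S1 and RBD-specific IgG titre, and the test product is a botanical immunomodulator. Other immune-active botanicals are therefore the co-exposure that the placebo arm most needs to be free of. The entry criteria recognise this, yet once a person is enrolled the advice turns towards AYUSH prophylaxis.

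Uptake is plausible. The Abstract states: "A large number of Indian people have been consuming various traditional medicines in the hope of better protection against COVID-19 infection". At stake are a clean description of the control condition, possible dilution of the treatment difference and, less importantly, consistent classification of such participants in the planned per-protocol analysis.

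**Working it through.** No figure in the plan is in dispute, so the check is a comparison of the texts, followed by a short argument on the direction of any effect.

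**Step 1: is the AYUSH advice limited anywhere?** No. The ordinary protective measures have their own sentence, so the AYUSH sentence reads as additional to them. No other section narrows it.

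**Step 2: does the protocol treat AYUSH interventions as things that can be ingested and can affect immunity?** Yes. The exclusion criterion covers AYUSH interventions used for prophylaxis or immune boosting and names AYUSH drugs among its examples. This shows that the category can include products. It does not show that the Ministry's guidelines recommend any.

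**Step 3: do the on-study rules settle the matter?** Only in part. Concomitant Medication covers herbal and home remedies, supplements, vitamins and minerals. It does not mention the AYUSH advice or claim precedence over it. Recording use in the CRF documents what was taken but does not decide whether it was allowed.

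**Step 4: direction of effect on the primary comparison.** Work on the log-titre scale, which the Analysis section prescribes. Let:

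- V = mean response to vaccine alone
- A = effect of Ashwagandha
- B = effect of a background AYUSH product
- u = proportion taking it, assumed equal in the two arms because the advice is identical and blinded
- k = fraction of A lost in a participant who also takes the background product (0 = effects add, 1 = complete overlap)

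Then:

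- Placebo mean = V + uB
- Ashwagandha mean = V + A + u(B − kA)
- Difference = A + u(B − kA) − uB = A(1 − uk)

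The documents give neither u nor k. Over the range from 0 to 1 for each:

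| Situation | u, k | Arm difference |
|---|---|---|
| Guidelines purely behavioural, or no uptake | u = 0 | A |
| Products taken, effects add | u > 0, k = 0 | A |
| Products taken, effects overlap | u > 0, 0 < k ≤ 1 | A(1 − uk), below A in size |
| Universal use, complete overlap | u = 1, k = 1 | 0 |

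The last row is a mathematical limit, not a forecast. Since B cancels, the shared background creates no spurious difference between arms. It does shift the placebo mean by uB, so when uB is not zero the control no longer shows the vaccine effect alone.

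**Step 5: reach.** The advice is addressed to every participant: 600 + 600 = 1,200 planned.

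**The case against.** The strongest reply is that no conflict has been shown. The guidelines are not reproduced. If they contain only behavioural measures, the two sections agree and nothing follows. Concomitant Medication is the section that governs what participants may swallow, whereas the AYUSH sentence sits in a general-care paragraph directly after masks and hygiene. Reading the general advice as subject to the specific rule is natural, and many sites would do so.

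The Abstract's remark on traditional medicine describes the Indian population. The trial sample is screened for recent use and told to abstain. Harm requires three things together: product-based guidelines, use despite the bar, and overlapping effects. None of these is quantified. The per-protocol set is not defined in the article, and its definition may properly be left to the full protocol or the analysis plan.

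Much of this stands. The conflict is conditional, no bias between arms is expected, no size can be given, and the per-protocol point is minor. The objection does not remove the two printed instructions or supply the missing precedence rule. This is not analytic detail that an article leaves elsewhere; it is advice to participants that the article states without limit. The natural reading is also only an inference, and one that sites could draw differently.

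**Conclusion.** The concern holds as a worthwhile, inexpensive correction. The AYUSH advice is unlimited as written and is not reconciled with the bar on other herbal remedies and supplements.

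The conclusion that the two instructions are unreconciled rests on the text alone. Any practical effect depends on assumptions the documents cannot confirm: that the guidelines include ingested products, that some participants take them, and, for dilution, that their effects overlap with those of Ashwagandha. Under equal uptake the intention-to-treat difference remains a valid comparison over whatever background exists. It is unchanged if effects add and moves towards zero if they overlap. No numerical size is claimed. Confidence is moderate because the guidelines' content is not available.

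**What to change.** Replace the AYUSH sentence in Trial Care and Record Retention, identically for both arms, with wording such as:

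> Ministry of AYUSH guidance will be followed only for measures that involve no herbal product, home remedy or supplement; the Concomitant Medication rules take precedence.

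Deleting the sentence is an acceptable alternative. Any AYUSH, herbal or supplement use should be entered in the concomitant-medication section of the CRF that already exists and reported by arm.

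The cost is a one-sentence amendment, which the protocol requires the ethics committees to approve before implementation. Because recruitment began in December 2021, a letter to sites is also needed so that participants already enrolled receive the corrected advice. Sample size, visits, assays and planned analyses do not change.

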## Discussion

Several vaccines have been approved in the first year of the pandemic on priority for an emergency use. We still do not have a clinically acceptable specific drug to treat COVID-19. The case fatality rate in India still hovers around 2% in the second pandemic year. It is indeed challenging to predict disease progression at an early stage. Agreeably, vaccination is reassuring, however the future remains somewhat uncertain. The success with vaccines is influenced by several host and environmental factors. The data on safety, tolerance and efficacy is not adequate. In case of natural COVID-19 infections it has been observed that the titers of IgG against spike protein may last for about 6 months, while the immunological memory may last up to 8 months (23, 24). However, the duration of protection after vaccination has not been established so far. A looming fear of more waves may sweep away some of the benefits of the vaccination in the population. The world indeed is immensely stressed and mental health is at stake (25). How to improve the performance of the vaccines remains a pivotal question. The current study protocol is planned and designed against this perspective.

Previous clinical studies have highlighted the role of humoral as well as cell-mediated immune responses in recovery from SARS-CoV-2 infection (26, 27). In previous studies the selective-Th-1 upregulating activity of Ashwagandha was demonstrated and in infection models, co-administration of Ashwagandha with DPT vaccine resulted in improved antibody titres against lethal challenge of pertussis toxins (8). *In silico* network ethnopharmacological investigations also suggest the ability of bioactive compounds of Ashwagandha to modulate immune pathways involved in innate and adaptive immune responses (28, 29). Further, the interim efficacy data for ChAdOx1 nCoV-19, evaluated in four trials across UK, Brazil and South Africa shows a protection of 64.1% after one standard dose (14). COVISHIELD^TM^ has been administered in two doses to a large population in India. We hypothesize that co-administration of Ashwagandha with the COVISHIELD^TM^ vaccine may enhance the antibody titres particularly after the first dose of the vaccine. A sustained long-term immune response to the vaccine has implications for prevention of reinfection. Therefore, the effect of Ashwagandha on the sustenance of neutralizing antibody titres up to 4 months after the second dose will also be evaluated in this study (30). Ashwagandha is also known to improve overall mental wellbeing.

Currently, the study involves the assessment of neutralizing antibodies against two well-characterized variants of concern (B1.617.2 and USA-WA1/2020 variants). Recently, a new variant B.1.1.529, named Omicron has emerged and it is likely that other newer variants may emerge during the course of the study. It would be interesting to evaluate the responses to these variants. As and when fully characterized BEI resources are available for new variants of concern, the investigators will take the decision to modify and make the necessary amendments to the protocol. Serum samples are being preserved at all time points of the study and may be used for such additional studies.

Our trial has the potential to have a significant impact on current vaccination program by improving immunogenicity, protection and general wellbeing with simple, safe and affordable intervention. In this trial we expect a beneficial effect beginning soon after the first dose of vaccination. We hope to investigate biological plausibility that the immune protection offered by a long-term co-administration of Ashwagandha may effectively address some of the vexing issues associated with the vaccination.

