# *HR-BHF: Health Related-Habits, Behavior and Fitness*.

@ *WHO QOL BREF: World Health Organization Quality of Life Instruments-short form*.

**Table 2 T2:** Schedule of laboratory investigations.

**Visit**	**Visit 0 Screening (Day −7 to −1)**	**Visit 1 Enrollment and randomization (Day 1)**	**Visit 2 (4 wks)**	**Visit 3: (8 wks)**	**Visit 4 (12 wks)**	**Interim analysis**	**Visit 5:(16 wks)**	**Visit 6** **Intervention completion** **(24 wks)**	**Visit 7: Part 1 completion (28 wks)**
CBC: blood hemoglobin, total and differential count, platelets Erythrocyte sedimentation rate (Westergren)	X				X			X	
D-dimer	X				X			X	
LFT: serum liver enzymes-SGOT, SGPT, alkaline phosphatase Serum albumin, globulin, bilirubin	X				X			X	
RFT: blood urea nitrogen Serum creatinine	X				X			X	
Blood sugar profile (BSL fasting and HbA1c)	X				X			X	
Urine routine	X				X			X	
^+^Urine pregnancy test	X		X	X	X		X	X	X
^#^RT-PCR throat/nose swab testing for SARS-CoV2 RNA	X		X	X	X		X	X	X
SARS- CoV-2 S1, RBD and N Specific IgG		X	X	X	X		X	X	X
sVNT					X			X	X
SNT (Wuhan isolate USA-WA1/2020 and Delta variant B1.617.2)					X				X

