# *RT-PCR throat nose swab test will be repeated in participants in case of development of any symptoms during the study duration*.

+ *for female participants*.

*Additional studies on measurement of secretory IgA and T cell responses are planned on a subset of the participants*.

If the vaccinated individual (after first or second dose) contracts COVID 19, then he/she shall be withdrawn from the study and will be treated under the supervision of COVID-19 physician till recovery. The participants who are withdrawn prematurely will be encouraged to continue follow up in a separate group as per the discretion and supervision of the study physician. The latter group will be permitted to use the current protocol methods and analyzed separately. All participants will be monitored for safety, immune response and occurrence of any breakthrough SARS-CoV-2 infection. An interim analysis at the end of 12 week is planned to evaluate the effect of Ashwagandha co-administration on safety and immune response following the first dose of the vaccine. The final analysis of data will be carried out after all the participants have completed the study at the end of 28 weeks.

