### Recruitment, Screening, Consent

Apparently healthy volunteers (18–45 years) who have received either the first or second dose of the COVID-19 vaccine as part of the Government of India vaccination programme will be included in this study. The study will include up to 300 participants who have received the first dose and at least 900 participants who have received the second dose. The investigator will be responsible for obtaining written informed consent from each participant prior to screening as per the national ethics guidelines (17). An information sheet in language best understood by the participant, giving details of the study will be provided to the participant for study and discussion if any with the investigator. Enough time will be given to the participant to make a voluntary decision to participate. Participant will be encouraged to ask questions and clear all doubts in a face to face interview with the investigator. After fully satisfying with the various provisions of the research study the participant will be asked to sign the consent form. Participants will be screened comprehensively by the study physicians for eligibility and to exclude any contraindication to participation in the study. If found eligible, participants will be randomized and enrolled. Participants will be followed up at predetermined time endpoints (eight visits including screening and completion visits) as per protocol till study completion (week 28).

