### Statistical Analysis

#### Sample Size and Power

The sample size is calculated based on the primary objective of improved immunogenicity of the vaccine with administration of Ashwagandha. Also, it was felt important to obtain a reasonably suitable (non-probabilistic) sample size for safety and tolerability. As there was no prior data on the expected effect size of the difference between the two study groups, a superiority margin of 7% was decided by expert consensus between the biostatistician (SS) and senior authors (AC, GT, [name], and BP). The sample size was calculated with 80% power and after consideration of interim analysis at the end of 12 weeks; assuming vaccine efficacy of 80% (22). The calculated sample size with the provision of one interim analysis was rounded to 600 subjects per study arms and totalling 1,200. The study will include upto 300 participants who have received the first dose and at least 900 participants who have received the second dose.

An interim analysis is planned after completing 12 weeks of intervention. The sample size of the study is decided based on the plan of one interim analysis. The sample size for interim analysis will be minimum 300 (with alpha = 2.96%).

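### One visit calendar serves two vaccine-entry groups, so the stated horizon of 4 months after dose 2 fits only the first-dose minority (at most 25%)

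*Protocol article*

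**What the plan says.** All places are in the protocol article.

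- **Entry groups.** Sample Size and Power gives a total "rounded to 600 subjects per study arms and totalling 1,200", made up of "upto 300 participants who have received the first dose and at least 900 participants who have received the second dose". Recruitment, Screening, Consent repeats the split.
- **Calendar.** Tables 1 to 3 place Day 1 at enrolment and randomisation, with visits at weeks 4, 8, 12, 16, 24 and 28. There is one schedule and no variant by entry dose. Under Trial Intervention, tablets are taken "beginning within 7 days of the first or second vaccine dose and continued up to 24 weeks". Study Design adds: "The final analysis of data will be carried out after all the participants have completed the study at the end of 28 weeks".
- **Assays.** Table 2 schedules IgG at every visit from Day 1, the surrogate neutralisation test (sVNT) at weeks 12, 24 and 28, and the neutralisation test (SNT) at weeks 12 and 28 only.
- **Horizon.** The Discussion states that "sustenance of neutralizing antibody titres up to 4 months after the second dose will also be evaluated in this study", without naming an entry group.
- **Interim.** Study Design gives the purpose of the week-12 interim as the effect on safety and immune response after the first vaccine dose.
- **Outcomes.** Secondary Outcome Measures lists how long the neutralising titre is sustained, with no time origin. It also has an infection time frame that starts at a Day 1 labelled as vaccination and closes at week 12 or dose 2, whichever comes first.
- **Randomisation.** The scheme is to take account of the first-dose and second-dose subsets.

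**The concern.** The horizon, the interim and the infection time frame all read as if everyone enrols after dose 1, receives dose 2 at about week 12 and is then followed for about 16 weeks. At least three quarters of participants enrol after dose 2 on that same calendar. A given visit therefore falls at a different time since dose 2 in each group.

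The groups also differ in what treatment could act on. First-dose entrants would receive dose 2 while taking tablets; second-dose entrants start tablets after it. An effect on the response to a dose taken on treatment is a different question from an effect on maintenance afterwards.

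At stake is interpretation. If the results are reported under the wording now in the article, week-28 titres will be described as persistence to 4 months when most of them are not, and a week-12 result will be described as a first-dose response when most participants entered after dose 2.

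**Working it through.** **Inputs.** Visit weeks (Tables 1 to 3); final visit at week 28; gap from entry dose to start of tablets of 0 to 7 days (Trial Intervention), written as a lag L of 0 to 1 week, taking Day 1 as the start of tablets; visit window of 7 days either side (Trial Intervention); 900 second-dose and 300 first-dose entrants of 1,200. The interval g between doses is not stated. I assume g = 12 weeks, suggested by the infection time frame in Secondary Outcome Measures, and show 4 to 16 weeks. One month = 365.25/12/7 = 4.348 weeks.

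**Formulas.** Weeks since dose 2 at study week v:
- second-dose entrants: v + L
- first-dose entrants: v − g + L

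**Step 1: reproduce the plan's 4 months.** First-dose entrants, g = 12, L = 0: 28 − 12 = 16 weeks, which is 16/4.348 = 3.7 calendar months or 4.0 four-week months. With L = 1: 17 weeks, 3.9 months. The figure reproduces for this group.

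**Step 2: second-dose entrants.** 28 + 0 to 28 + 1 = 28 to 29 weeks, or 28/4.348 = 6.4 to 29/4.348 = 6.7 months. With the visit window the range is 27 to 30 weeks (6.2 to 6.9 months). This needs no assumption about g. Share affected: 900/1,200 = 75%, a minimum.

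**Step 3: sensitivity to g (first-dose entrants, week 28, L = 0).**

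| g (weeks) | Weeks since dose 2 | Months |
|---|---|---|
| 4 | 24 | 5.5 |
| 8 | 20 | 4.6 |
| 12 | 16 | 3.7 |
| 16 | 12 | 2.8 |

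Within this range the first-dose horizon never reaches 28 weeks.

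**Step 4: each visit, in weeks since dose 2 (g = 12).**

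| Visit week | Second-dose entrants (L = 0 to 1) | First-dose entrants (L = 0) | Neutralisation assay |
|---|---|---|---|
| 4 | 4–5 | −8 | none |
| 8 | 8–9 | −4 | none |
| 12 | 12–13 | 0 | sVNT, SNT |
| 16 | 16–17 | 4 | none |
| 24 | 24–25 | 12 | sVNT |
| 28 | 28–29 | 16 | sVNT, SNT |

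At equal lag the groups differ by the whole dose interval at every visit.

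**Step 5: where 4 months falls for second-dose entrants.** 4 × 4.348 = 17.4 weeks after dose 2, which is study week 16.4 to 17.4 after subtracting the lag. The nearest visit is week 16, where Table 2 has IgG but neither sVNT nor SNT. The SNT samples also differ in meaning: at g = 12 the week-12 sample falls at about dose 2 in first-dose entrants, leaving them one clearly post-dose-2 SNT, whereas second-dose entrants have two.

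**Step 6: the interim.** At week 12, second-dose entrants are 12 to 13 weeks past dose 2, so a description of it as following dose 1 does not fit them.

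**The case against.** The case on the other side has real force.

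- **The treatment contrast is not biased.** Allocation is randomised and the scheme takes dose group into account, so the mix of times since dose 2 should be balanced between arms. This stands.
- **No follow-up is lost.** The 4 months appears in a Discussion sentence, the outcome itself carries no 4-month limit, and second-dose entrants are followed beyond it. Their sVNT samples at weeks 12 and 24 bracket the 4-month point, and the Discussion says serum is kept from all time points. This also stands: for this group the horizon is understated. It is still a wrong description of what most participants contribute.
- **The interim might be meant for first-dose entrants only.** The document does not say so. Sample Size and Power sets a minimum of 300 for the interim and a maximum of 300 first-dose entrants, so that reading works only if exactly 300 enrol and all count at week 12.

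Three stronger readings are tempting, and the document does not support them:

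1. A reader might blame the counting of visits from enrolment. Tablets start within 7 days of the entry dose, so that clock adds only 0 to 1 week. Counting from the entry dose would leave the mismatch in place; its source is two entry doses on one calendar.
2. A reader might infer that the plan pools each visit across all participants. The Analysis section names tests and log transformation but is silent on pooling, on entry group and on time origin. A statistical analysis plan may settle these, and the silence is not a fault here.
3. A reader might set the antibody decay over the roughly 12-week offset against a treatment effect. Such decay separates the entry groups, not the arms. The document gives no half-life, and it says there was no prior information on effect size.

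**Conclusion.** The point holds as a mismatch between stated descriptions and the schedule. For at least 75% of participants the final neutralisation sample falls 6.4 to 6.7 months after dose 2, not 4, and no neutralisation assay is scheduled at the visit nearest 4 months. The stated horizon and the account of the interim fit only first-dose entrants, at most 300/1,200 = 25%.

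The second-dose figures rest on the printed calendar and on Day 1 being the start of tablets. The first-dose figure of 3.7 to 3.9 months rests on an assumed 12-week interval; for 4 to 16 weeks at zero lag it runs from 5.5 down to 2.8 months.

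The consequence is limited to what the titre, interim and duration-of-sustenance results mean. It is not a claim of bias between arms or of lost data. It should be corrected, because without a time origin the sustenance outcome cannot be read.

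**What to change.** 1. State the horizon by entry group: about 4 months after dose 2 for first-dose entrants (given a 12-week interval) and about 6.5 months for second-dose entrants. Reconcile the interim description in Study Design, the Day 1 and week-12 time frame in Secondary Outcome Measures, and the Discussion sentence with Tables 1 to 3.
2. Index persistence of IgG and neutralising titre by weeks since dose 2, using the vaccine use that the Compliance section already has logged.
3. Stratify the treatment comparison by entry-dose group, and show the effect in each group beside any combined estimate.

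The cost is wording and analysis programming, with no new visits. The downside is wider intervals in the first-dose group: at most 300 participants allocated 1:1, so about 150 per arm. If a neutralising titre close to 4 months is wanted in second-dose entrants, the stored week-16 serum could provide it at the price of extra assays; the three changes above do not depend on that.
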